## Abstract

**Background:**

Shoulder pain of musculoskeletal origin is the main cause of upper limb pain of non-traumatic origin. Despite being one of the most common reasons for consultation, there is no established protocol for treatment due to the complexity of its etiology. However, it has been shown that the presence of myofascial trigger points on the shoulder muscles is a common condition associated with patients suffering from shoulder pain. This protocol has been created which describes the design of a randomized controlled trial to evaluate the effectiveness of the inclusion of dry needling (DN) within a protocol of manual physiotherapy and therapeutic exercise in the treatment of chronic shoulder pain of unspecific origin.

**Methods:**

Thirty-six participants aged 18–65 years will be recruited having mechanical chronic shoulder pain on unspecific origin and meeting the inclusion criteria. These will be randomized to one of two interventions, (i) DN, manual physiotherapy and therapeutic exercise or (ii) sham DN, manual physiotherapy and therapeutic exercise. The protocol will cover 6 weeks of treatment, with a 6-month follow-up. Our main outcome measure will be the Visual Analogue Scale for pain.

**Discussion:**

This is the first study to combine the use of DN, manual physiotherapy and an exercise program with a 6-month follow-up, thus becoming a new contribution to the treatment of chronic shoulder pain, while new lines of research may be established to help determine the effects of DN on chronic shoulder pain and the frequency and proper dosage.

**Trial registrations:**

International Standard Randomized Controlled Trial Number Register: ISRCTN30604244 (http://www.controlled-trials.com) 29 June 2016.

## Background

Shoulder pain is a common musculoskeletal problem, with an annual prevalence of 20 to 50%, being the main cause of non-traumatic upper limb pain. It presents a high chronicity and recurrence [1] and the symptoms persist for 6 to 12 months in 40 to 50% of patients [2]. However, there is no standard for the clinical definition of shoulder pain [3].

Clinical trials tend to use the term nonspecific shoulder pain due to the lack of agreement on diagnostic criteria, lack of specificity of clinical evidence, coexistence of multiple shoulder pathologies and lack of any diagnostic test that is considered a “gold standard” [4]. The most common signs and symptoms are localized in the deltoid, forearm and shoulder region, presenting shoulder stiffness and limited range of motion [5] which restrict daily living activities [6].

Shoulder Impingement Syndrome is the most common diagnosis in primary care [7–9] and although it is believed to be the cause of shoulder pain, there is no solid evidence to support this. Furthermore, the presence of calcifications, acromial bone spurs, subacromial swelling, degenerative rupture of the rotator cuff, tendon inflammation and signs of degeneration are prevalent in both healthy subjects and in subjects with shoulder pain [10–12] so its diagnosis alone would not justify the presence of symptoms.

Moreover, it has been shown that the presence of myofascial trigger points (MTrPs) in the shoulder muscles is a common condition in patients with shoulder pain [3], and may cause pain during muscle stretching, contraction or compression. These MTrPs are hyperirritable points in taut bands of skeletal muscle and are painful to compression, producing motor dysfunction and referred pain [13].

As many as 17 muscles are known to reproduce similar symptoms to those of other painful shoulder syndromes, including pain at rest, upon movement and sleep disorders [1, 13, 14]. Therefore, the presence of MTrPs has been suggested as an alternative explanation for shoulder pain, regardless of the presence of subacromial disorders [1, 14].

Treatment of shoulder pain usually begins with conservative therapies such as rest, physical therapy, anti-inflammatory drugs (NSAIDs) and corticosteroid injections [15, 16]. However, current studies have shown the benefits of a multimodal treatment for shoulder pain including techniques such as dry needling, stretching, manual therapy, mobilization techniques, applying cold, home exercise, ischemic compression of MTrPs and ergonomic recommendations [1, 17].

The choice of treatment is often subjective and depends on the therapist’s skill and training, while therapeutic exercise programmes in combination with manual therapy techniques often show good results [5, 18]. A recent meta-analysis by Kietrys et al. [5] recommends using dry needling, compared against placebo, to reduce pain, following treatment, and at 4 weeks follow-up in patients with Myofascial Pain Syndrome of the Upper Quadrant. However, new studies to support this recommendation are required.

It has been suggested that the inclusion of dry needling, in a single session, within a multimodal physiotherapy programme for patients with post-surgery shoulder pain, produces improvements in on and range of motion [19]. However, we have not found similar studies in patients with chronic shoulder pain of unspecific origin.

Therefore, the main aim of this study is to determine the effectiveness of including dry needling in a manual physiotherapy and therapeutic exercise programme, for the treatment of chronic shoulder pain of unspecific origin. Our hypothesis is that by including a single session of dry needling in a manual physiotherapy and therapeutic exercise programme, treatment outcomes improve, reducing symptoms and improving function in patients with shoulder pain.

## Methods

### Design

Study protocol for a randomized controlled parallel group single-blind trial. This study was registered with the International Standard Randomized Controlled Trial Number (ISRCTN30604244) and complies with the recommendations of The SPIRIT 2013 Statement.

Participants will be randomized to receive dry needling, either real or sham. Allocation to either group, namely real or sham dry needling, will be achieved through a computer-generated sequence of random numbers. The allocation sequence is created and carried out by a non-interventionist physiotherapist, in charge of telephone screening and of handling the data obtained in the various assessment sessions.

Figure 1 shows a flowchart of the progress of the various stages of this test. This study was approved by the Committee on Human Research, Universidad de Alcalá (Reference: CISM/HU/2015/19).

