### Participants

From the town of Alcalá de Henares (Madrid), aged between 18 and 65 years with chronic mechanical shoulder pain of unspecific origin, lasting at least 3 months and provided they give their consent after being informed about participation in the study. The recruitment of participants will be conducted via email for University of Alcalá workers and students and by placing posters in a number of social and sports centres around the city of Alcala de Henares, where information about the study and contact information will be provided. Subsequently, a first telephone interview will be conducted to clarify any doubts of the participants, and the first screening for inclusion in the study will be carried out.

Participants’ personal data will be numerically coded and stored in a computer database, which may only be accessed to by the physiotherapist in charge of participant randomization and blinding.

Informed consent, as well as all study information will be emailed to the participants. Subsequently, prior to data collection and baseline measurement, participants should sign the informed consent, which could be revoked at any time during the intervention.

Inclusion criteria:Chronic mechanical shoulder pain of unspecific origin lasting at least 3 months.Aged between 18 and 65 years.Presence of active trigger points or areas of mechanical hypersensitivity in the muscles to be treated (upper trapezius, infraspinatus, subscapularis and middle deltoids) with pain reproduced in one or more muscles.

Participants will be examined for the presence of active trigger points in the muscles selected by a clinician with more than 10 years of experience in the treatment of MTrPs. Diagnosis of MTrPs will be determined by the presence of the following criteria: [1] hypersensitive point in a palpable taut band, [2] visible or palpable local spasm in response to MTrP palpation, and [3] reproduction of referred pain by palpation of the sensitive spot. These criteria have shown good interexaminer reliability (κ, kappa between 0.84 to 0.88) when applied by an experienced evaluator [20].

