### Research team

This study will involve 7 physiotherapists; 1 Clinical physiotherapist with more than 10 years of experience in the use of dry needling for MTrP treatment, 2 evaluator physiotherapists and 2 physiotherapists responsible for carrying out the manual physiotherapy and therapeutic exercise treatment of the participants, one physiotherapist responsible for the interview, initial screening and randomization of participants, and one physiotherapist who will perform the statistical analysis.

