### Randomization and blinding

At baseline, the non-interventionist physiotherapist, through the Random Allocation Software, will randomize by permuted blocks [4, 8], the participation of the 5 intervening physiotherapists with respect to a sample of 36 participants. The physiotherapist in charge of performing dry needling –which may be A (experimental) or B (control)- and 2 groups of 2 physiotherapists, G1 and G2, with an evaluator and a therapist in each group. 4 possible treatment groups (AG1, AG2, BG1, BG2) will be obtained evenly in each randomization block.

Participants who successfully pass the phone screening will be assigned a number on the randomization table in order of inclusion in the study; the treatment group (A or B) and physiotherapist group (G1 or G2) in which they will be included are specified. The physiotherapist responsible for carrying out the dry needling, will provide a list with the names of the participants, showing the type of intervention that each will receive (A or B).

Each participant will receive a single dry needling or sham dry needling intervention at the start of the first treatment session, conducted by a physiotherapist with more than 10 years of experience in MTrP treatment with dry needling. Said physiotherapist will be blinded to the baseline data of participants. On the other hand, both the physiotherapists who evaluate the participants and those who perform manual physiotherapy treatment and therapeutic exercise, will be unaware of the group of each participant.

In addition, data collected during the assessment of participants will not be revealed to the physiotherapists who perform the treatment, and participants will be instructed not to disclose their experience and information related to the first treatment session of dry needling.

Lastly, the physiotherapist responsible for the statistical analysis will be blinded. Once the intervention is finished he will receive a data table in excel with all the necessary data in binary code.

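### The physiotherapist who holds the allocation sequence is also assigned the handling of the assessment data, which leaves an unblinded link between blinded evaluators and a blinded statistician

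*Protocol article*

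**What the plan says.** **Sequence.** Under Design: "The allocation sequence is created and carried out by a non-interventionist physiotherapist". The same sentence continues that this person is "in charge of telephone screening and of handling the data obtained in the various assessment sessions". No outcome and no visit is excepted.

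**Randomisation and codes.** Randomization and blinding gives the task to the same role: "the non-interventionist physiotherapist, through the Random Allocation Software, will randomize by permuted blocks". The codes are not masked, since the needling assignment is described as one "which may be A (experimental) or B (control").

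**Who is blinded.** The same section blinds the evaluators and the treating physiotherapists to group, the needling physiotherapist to baseline data only, and the statistician. The sequence holder is not on that list. For the statistician it adds: "Once the intervention is finished he will receive a data table in excel with all the necessary data in binary code".

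**Team.** Research team lists seven physiotherapists, including "one physiotherapist responsible for the interview, initial screening and randomization of participants". None of the others is described as a data manager.

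**Database.** Participants says that the numerically coded personal data sit in a database "may only be accessed to by the physiotherapist in charge of participant randomization and blinding". That sentence is about personal data, not outcomes.

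**The concern.** The plan blinds both ends of the data chain: the people who measure and the person who analyses. The stage in between is assigned to the one non-treating team member who must know the allocation. If handling includes any reading, scoring, querying or cleaning, knowledge of the arm could influence values before the statistician sees them. The statistician, who receives a prepared table, would not see that from the table alone.

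The article describes steps that somebody must carry out between the visit and the table. A VAS mark on a 100-mm line has to be converted to a number. A DASHe form is invalid with four or more unanswered items. Triple pressure-threshold and range-of-motion readings are averaged. The primary outcome is the VAS, so a net shift between arms at this stage would go straight into the primary comparison.

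**Working it through.** **Step 1: the role assignments side by side.** The article gives no figure to reproduce here, so the main check is to follow the data.

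| Stage | Who | Blinded to arm? | Section |
|---|---|---|---|
| Create and run the sequence | Non-interventionist physiotherapist | No, holds it | Design; Randomization and blinding |
| Measure outcomes | Two evaluators | Yes | Research team; Randomization and blinding |
| Handle assessment data | The same non-interventionist physiotherapist | Not listed as blinded, and holds the sequence | Design |
| Build the Excel table | Not named | Not stated | Randomization and blinding |
| Analyse | Statistician | Yes | Randomization and blinding |

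The first and third rows name the same person in one sentence, and the codes are tied openly to experimental and control. That part is stated text. That this person also builds the table is an inference: no other role is given the data, but the article does not say it.

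**Step 2: how much a shift would matter.** This is a sensitivity calculation and does not predict that bias will occur.

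Inputs:
- n per arm: 14 (28/2) and 18 (36/2), from Sample size.
- Two-sided alpha 0.05, from Sample size and Statistical analysis.
- SD of VAS change 20 and 25 mm: assumed, not in the article.
- Net arm-related shift δ of 0.5, 1, 2 and 5 mm: assumed, not in the article. Against the 13 mm minimal difference under Primary outcome measures, 2 mm is 2/13 = 15% and 5 mm is 5/13 = 38%.
- Comparison at one visit by a t test for two independent groups, with no true effect: assumed.

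Formulas: df = 2n − 2; noncentrality λ = δ / (SD × √(2/n)); critical value c = t(0.975, df). The favourable tail is P(T > c) and the two-sided error is P(T > c) + P(T < −c), with T noncentral t(df, λ).

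Worked example, n = 18, SD 20, δ = 5: df = 34, c = 2.032, λ = 5 / (20 × √(2/18)) = 5 / 6.667 = 0.75. Upper tail 0.109, lower tail 0.004, total 0.113.

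Two-sided error, with the tail favouring needling in brackets:

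| n per arm, SD | δ = 0.5 mm | δ = 1 mm | δ = 2 mm | δ = 5 mm |
|---|---|---|---|---|
| 14, 25 mm | 5.0% (2.8%) | 5.1% (3.2%) | 5.5% (4.0%) | 8.0% (7.4%) |
| 14, 20 mm | 5.1% (2.9%) | 5.2% (3.3%) | 5.8% (4.4%) | 9.8% (9.3%) |
| 18, 25 mm | 5.0% (2.9%) | 5.2% (3.3%) | 5.6% (4.2%) | 9.0% (8.4%) |
| 18, 20 mm | 5.1% (3.0%) | 5.2% (3.5%) | 6.0% (4.8%) | 11.3% (10.9%) |

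The nominal values are 5% two-sided and 2.5% in one tail. For a shift up to 1 mm the two-sided error hardly moves. It reaches about 8–11% only at 5 mm, which would need a consistent one-directional error across patients.

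**Step 3: release timing.** The statistician's table is due when the intervention ends. The text on home exercise, under the manual physiotherapy and exercise programme, places the end of the intervention before the 6-month evaluation. The same blinding sentence promises all the necessary data, however, and Statistical analysis uses the 6-month measurement. A complete table therefore cannot precede that visit. The wording is loose and worth tidying, but it does not show an early release.

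**The case against.** The best defence is that handling may mean no more than custody, coding and transfer. The article does not say who reads the VAS line, who scores the DASHe or who averages the triple readings, and it does not mention query resolution at all. Scoring by the two blinded evaluators fits the text equally well. The steps also leave little room for judgement: averaging is arithmetic, the DASHe limit is a fixed count, and reading a line is a ruler measurement. All of this stands.

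Three stronger readings are tempting, and the article supports none of them:

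- A reader might infer that every outcome is in fact processed by someone who uses knowledge of the arm. The article shows the opportunity only.
- A reader might infer that such a shift could never be found later. The VAS marks and questionnaires are source records that could be re-read, and nothing says they are discarded.
- A reader might take the restricted database under Participants as proof that this person alone holds the outcomes. That sentence covers personal data.

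It can also be said that entry rules, database lock and key transfer are data-management detail that an article leaves to the full protocol. Their absence is indeed no finding. The combination of the two roles is different, because the article states it outright.

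**Conclusion.** The point holds as a stated combination of roles. One physiotherapist, who knows each participant's arm, is assigned both the allocation sequence and the handling of the assessment data, and is not among the blinded roles. Measurement and analysis remain protected by the blinding of evaluators and statistician, so the exposure is confined to the stage between them.

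The size of the exposure cannot be derived from the article. Under the assumptions above, the two-sided error at one visit lies between about 5.0% (0.5 mm shift) and about 11% (5 mm shift). Quoting only the favourable tail at 2–5 mm, about 4–11% against 2.5%, would give too strong an impression: the test is two-sided and nothing in the article supports a shift of that size. This is a cheap improvement worth making, not a demonstrated flaw in the result.

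**What to change.** - **Design:** reword so that the holder of the allocation sequence does not score, enter or clean outcome data.
- **Data entry:** the two blinded evaluators score the outcomes and enter them under the study number.
- **Lock and key:** the file is locked after the last 6-month evaluation. Only then does the sequence holder pass the statistician the coded arm key.
- **Randomization and blinding:** replace the release condition, now tied to the end of the intervention, with *after the last 6-month evaluation and data lock*.

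The cost is a few sentences of protocol wording and a few minutes of data entry per visit by staff already in the team. No new personnel are needed.

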**Fig. 1 Fig1:**
[figure not shown]
Study Flowchart. Stages of the intervention protocol

### Participants

From the town of Alcalá de Henares (Madrid), aged between 18 and 65 years with chronic mechanical shoulder pain of unspecific origin, lasting at least 3 months and provided they give their consent after being informed about participation in the study. The recruitment of participants will be conducted via email for University of Alcalá workers and students and by placing posters in a number of social and sports centres around the city of Alcala de Henares, where information about the study and contact information will be provided. Subsequently, a first telephone interview will be conducted to clarify any doubts of the participants, and the first screening for inclusion in the study will be carried out.

Participants’ personal data will be numerically coded and stored in a computer database, which may only be accessed to by the physiotherapist in charge of participant randomization and blinding.

Informed consent, as well as all study information will be emailed to the participants. Subsequently, prior to data collection and baseline measurement, participants should sign the informed consent, which could be revoked at any time during the intervention.

Inclusion criteria:Chronic mechanical shoulder pain of unspecific origin lasting at least 3 months.Aged between 18 and 65 years.Presence of active trigger points or areas of mechanical hypersensitivity in the muscles to be treated (upper trapezius, infraspinatus, subscapularis and middle deltoids) with pain reproduced in one or more muscles.

Participants will be examined for the presence of active trigger points in the muscles selected by a clinician with more than 10 years of experience in the treatment of MTrPs. Diagnosis of MTrPs will be determined by the presence of the following criteria: [1] hypersensitive point in a palpable taut band, [2] visible or palpable local spasm in response to MTrP palpation, and [3] reproduction of referred pain by palpation of the sensitive spot. These criteria have shown good interexaminer reliability (κ, kappa between 0.84 to 0.88) when applied by an experienced evaluator [20].

Exclusion criteria:Previous surgery on the shoulder.Previous history of shoulder dislocations.Whiplash.Cervical radiculopathy.Diagnosis of fibromyalgia.Diabetes.Needle phobia or any contraindication to dry needling (e.g. anticoagulants or psychiatric disorders).Bilateral shoulder pain.Pregnancy.Having received dry needling in the last 6 months.Currently receiving other physiotherapy treatment for shoulder pain.

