### Dry needling of myofascial trigger points

To perform the dry needling procedure, patients should be placed on: their healthy or good side for infraspinatus and deltoids muscle; supine decubitus for subscapularis muscle; and prone decubitus for upper trapezius muscle. The physiotherapist will treat each MTrP that have previously been located in the muscles: upper trapezius, infraspinatus, subscapularis and middle deltoid.

After this, a 0.30x40mm monofilament needle (AGUPUNT, APS®) will be inserted towards the muscle mass. Said needle should be inserted into and extracted from the muscle using the “fast in and fast out” technique [23]. Needle insertion will be repeated 12 times in each muscle, the dry needling procedure being similar to that used by Hong [23, 24]. At most one MTrP (the one producing most pain) in each of the muscles will be needled. If no MTrP is found during muscle palpation, the needling procedure will not be performed on that muscle.

Meanwhile, the control group will receive the same treatment but using 0.30x30mm sham needles (Streitberger Placebo - needle®, Asiamed), which have been used before in another study [25].

Participants in both groups, will receive the same information about the sensations of dry needling procedure. They will be informed, at the beginning of the technique, that they may or may not feel the introduction of a needle through the skin. This will be related to the area of the body where the puncture is performed and according to the sensitivity of the subject. Afterwards, they will feel as the physiotherapist manipulates the needle with his hand repeatedly. In addition, participants should communicate to the physiotherapist the sensations they notice during the performance of the technique.

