### Statistical analysis

Data analysis will be carried out following the evaluation standards of the design of experimental studies with a control group. The experimental group (dry needling + manual physiotherapy and therapeutic exercise) will be compared with the control group (sham dry needling + manual physiotherapy and therapeutic exercise).

Data will be analysed using SPSS v.22 software for Windows. All statistical tests will be carried out considering a confidence interval of 95% (*p*-value <0.05) to determine the effectiveness of the 2 interventions by the method of intention to treat. Prior to statistical comparisons, all data will be analysed to determine the distribution of normality by the Shapiro-Wilk test. Subsequently, the homogeneity of the two intervention groups will be studied using Student’s t test for independent samples for data conforming to normal and the Mann-Whitney test for data that do not. The sex variable will be studied through Pearson χ2 or Fisher’s exact test, if the former cannot be used. Then a descriptive analysis of the data for the dependent variables will be performed. In these analyses, the mean and standard deviation (SD) for the dependent variables with normal distribution will be calculated. For variables that do not conform to normal, the data will be expressed with the median and first and third quartiles.

For the sex variable, frequencies are used. The existence of differences within each group will be determined, taking into account each group in isolation, between the different measurements (baseline and one week after dry needling; and post-treatment: at one week, at one month, at 3 months and at 6 months) in each of the study variables. In the VAS variable, measurements will also be taken in the treatment sessions; 2nd week, 3rd week, 4th week, 5th week, 6th week, using ANOVA for repeated measures, supplemented with simple and Helmert-type contrasts for variables that follow normal or Friedman’s ANOVA test, supplemented by Dunn’s multiple comparison test for those variables that will not conform to normal. ANCOVA will be performed to see the effect through different analyzes of the results and to intensify statistical power of the study. For this, the existence of a linear relationship and the homogeneity between the crude and basal scores of the dependent variables will be previously studied.

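### The eligibility criterion, the needling rule and the delivery statement do not fit together: a patient can be randomised without a trigger point and receive neither real nor sham needling

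*Protocol article*

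**What the plan says.** All of the relevant text is in the Methods of the Protocol article.

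- **Participants, inclusion criteria.** Patients need "Presence of active trigger points or areas of mechanical hypersensitivity in the muscles to be treated" (four muscles are named), with pain reproduced in at least one muscle.
- **Participants, diagnosis.** "Diagnosis of MTrPs will be determined by the presence of the following criteria: [1] hypersensitive point in a palpable taut band", followed by a local spasm on palpation and reproduction of referred pain. The three items are joined by *and*.
- **Dry needling of myofascial trigger points.** "If no MTrP is found during muscle palpation, the needling procedure will not be performed on that muscle". In the other arm, "the control group will receive the same treatment but using 0.30x30mm sham needles", so the same rule governs the sham procedure.
- **Randomization and blinding.** "Each participant will receive a single dry needling or sham dry needling intervention at the start of the first treatment session". On timing: "Participants who successfully pass the phone screening will be assigned a number on the randomization table in order of inclusion in the study", with the arm already specified in that table.
- **Statistical analysis.** Data are analysed "to determine the effectiveness of the 2 interventions by the method of intention to treat".

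**The concern.** The entry criterion has two branches, and the procedure is tied to only one of them. A patient who enters through the hypersensitivity branch and has no qualifying MTrP in any of the four muscles meets the criteria for randomisation but not the condition for being needled, with either needle. No text says what happens to such a patient, and the statement that each participant receives one of the two procedures cannot then be true.

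The trial estimates what dry needling adds to manual physiotherapy and exercise. A patient who gets neither procedure has the same care in either arm and contributes nothing to that contrast. Under intention to treat the patient still counts, so the estimated difference moves towards zero. With 36 patients there is little room for this: two such patients among the 18 in each arm would be 2/18 = 11%.

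**Working it through.** **Step 1: follow one patient through the text.** Take a patient with a painful, hypersensitive area in one of the four muscles but no palpable taut band or no local spasm.

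| Question | Section | Answer |
|---|---|---|
| Eligible? | Participants, inclusion criteria | Yes, through the second branch |
| Has an MTrP? | Participants, diagnosis | No, the three criteria are not all met |
| Needled or sham-needled? | Dry needling | No, the muscle is omitted in both arms |
| Receives one of the two procedures? | Randomization and blinding | Stated to be yes for every participant |
| In the analysis? | Statistical analysis | Yes, by intention to treat |

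The third and fourth answers conflict.

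**Step 2: timing.** Numbers on the randomisation table go to those who pass the phone screening, and an MTrP cannot be palpated by telephone. The text adds that numbers follow the order of inclusion, so palpation may in practice come first, but no sentence requires it.

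**Step 3: dilution.** Let p be the share of patients with no qualifying MTrP, expected to be equal in the two arms. If needling has zero effect in them and the full effect in everyone else, the mean difference becomes (1-p) times its size. To hold power, the sample size must rise by about 1/(1-p)²: 1.11 at 5%, 1.23 at 10% and 1.56 at 20%. The document gives no p. These values are assumptions.

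**Step 4: reproduce the planned sample size.** Inputs from the Sample size section: effect size 0.25 (taken as Cohen's f), correlation ρ = 0.5, m = 6 measurements, k = 2 groups, sphericity correction ε = 0.5, α = 0.05, power 0.95, N = 28. For the repeated-measures ANOVA interaction:

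- λ = f² · N · m · ε / (1-ρ)
- df1 = (k-1)(m-1)ε and df2 = (N-k)(m-1)ε

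With ε = 1: λ = 0.0625 × 28 × 6 / 0.5 = 21, df = 5 and 130, power 0.954. This returns the stated 28. With the stated ε = 0.5: λ = 10.5, df = 2.5 and 65, power 0.785, and N = 46 would be needed for 0.95. That mismatch is a separate matter, so both settings are carried forward.

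**Step 5: power with f replaced by 0.25(1-p).**

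| p (assumed) | f | Power at 28, ε = 1 | N for 0.95, ε = 1 | Power at 28, ε = 0.5 | N for 0.95, ε = 0.5 |
|---|---|---|---|---|---|
| 0 | 0.25 | 0.954 | 28 | 0.785 | 46 |
| 5% | 0.2375 | 0.929 | 32 | 0.738 | 50 |
| 10% | 0.225 | 0.897 | 34 | 0.687 | 56 |
| 20% | 0.20 | 0.802 | 44 | 0.576 | 70 |

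**The case against.** The strongest reply is that the authors treat a hypersensitive area and an MTrP as the same thing. Table 1 supports this: its MTrP technique is aimed at the most hyperalgesic point of the same four muscles, is dropped where there is no MTrP, and the next row refers back to that target as the hyperalgesic point. The omission rule is also written per muscle, which fits a criterion asking for reproduced pain in one or more muscles. An experienced clinician examines for active trigger points, and the statement that each participant receives a procedure suggests that everyone was expected to have a target. This probably describes the intention, but the wording does not secure it. The criterion joins two alternatives with *or*, the definition demands three findings, and reproduced pain requires neither a taut band nor a local spasm. Nothing guarantees one qualifying muscle per patient.

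Three further replies stand in full:

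- **Frequency.** A reader might infer that some randomised patients will go without either procedure. The document does not show this. It shows only that they can.
- **Bias and blinding.** A reader might infer a directional bias or unmasking. The omission rule is the same in both arms. A patient on whom nothing was done may notice it, but learns nothing about the allocated arm. What remains is attenuation.
- **Power.** The figures belong to the repeated-measures F test of the sample size section. The planned comparison between groups uses differences from baseline, by t test or Mann-Whitney test. The factor (1-p) applies to a mean difference under any of these tests, but the power values do not carry over. They also assume 28 completers. If all 36 stayed, the ε = 1 figures would be 0.988 with no dilution and 0.979, 0.963 and 0.905 at 5, 10 and 20%.

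**Conclusion.** The inconsistency holds on the text: eligibility, delivery of the procedure and the statement that everyone receives it cannot all be true for a patient who enters on hypersensitivity alone and has no qualifying MTrP. Such a patient would stay in the intention-to-treat comparison and could dilute it by (1-p), equally in both arms.

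The size is unknown, because p is not given and may be zero. The power losses in the table are illustrations that rest on an assumed p, a zero needling contrast in these patients, a full effect in the others, and the model of the sample size section. They do not show that the trial will lose that power. The point merits correction because the gap is easy to close before enrolment and cannot be undone once such patients are randomised.

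**What to change.** Reconcile the three sections (Participants, Randomization and blinding, Dry needling) so that everyone randomised can receive the allocated procedure. On the eligibility side this takes two changes:

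1. **Match the criterion to the definition that triggers the procedure.** Either require at least one MTrP meeting the three listed criteria in one of the four muscles, or state explicitly that the two terms mean the same thing.
2. **Assign the randomisation number after the palpation examination** that the Participants section already plans, rather than after the phone screening.

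The rule on which muscles are needled is left to the sponsor's clinicians.

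The cost is a possibly slightly narrower population and a small change in the order of procedures. The second item changes the assignment sequence, so the fix is more than the edit of one phrase. If the two terms were always meant as equivalent, the first item changes wording only.
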